To implement an RDS, a number of assumptions have to be met, including that the activities which constitute membership in the population (in this case abortion) must create connections amongst the members of the population, that the members must share active ties, and that the trait defining the population is objectively verifiable [10]. When these assumptions are met, there is no transmission bias. To verify the extent to which these assumptions are met in the case of abortion, we conducted in 2018 a systematic review of the literature on information sharing by abortion seekers in low and middle-income countries since 2000, which generated 79 studies for inclusion [20]. An analysis of these articles shows that disclosure to network members (beyond the partner and family) depends on the context of abortion service provision and on the level of stigma. Where women can access abortions (whether legal or not) *anonymously* (through ads, flyers, internet, etc.), abortion seekers do not need to disclose beyond their family members, and do not if stigma is strong. For example, qualitative interviews with unmarried women in Ethiopia showed that they managed to access (legal and illegal) services without revealing their situation to anyone they knew [35]; same for legal service users in Colombia [36]. On the other hand, in contexts where abortion services (whether legal or not) *cannot be accessed anonymously*, women (or their family members) *have* to reach out to members of their network -especially recent abortion seekers- to locate an abortion provider or method. Abortion stigma, while often high, is dealt with by disclosing only to members of the network bound to secrecy. The vast majority of sites described in the systematic review, and this in all the world regions (Africa, Asia, Latin America), fell in this category. For instance, in Saudi Arabia, 82% of self-reported misoprostol users in a survey knew another misoprostol user [37]; in Brazil, 1 year after the abortion, 70% of teenage post-abortion care users reported knowing a friend who had terminated [38]; an illegal abortion provider in a qualitative study in Kenya confirmed that prior clients were the major source of new clients [39]; etc. Moreover, the review reveals that the diffusion of medical abortion does not seem to make women less dependent on their network, because information on medical abortion is not available anonymously and publicly in these low and middle-income contexts. The existing literature thus confirms that the assumptions of the RDS (no transmission bias) are met for a large majority of recent abortion seekers (in the order of magnitude of 7 or 8 abortion seekers out of 10), *but only in contexts where abortion services cannot be accessed anonymously*.^4^ In fact, one RDS experiment in South Africa, where abortion services even in the informal sector are advertised on flyers, posters etc., seemed less successful as it yielded only 43 cases of women who had an informal sector abortion, a third of which were female sex workers [40].

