
Over the years, methodological improvements have been developed regarding how RDS studies are designed, data is collected and statistical estimates are generated. These developments include managing the flow of participants into the study by utilizing a systematic coupon reduction process which is the reduction of the number of coupons to be distributed (from 3 to 2 and then from 2 to 1) at some specific waves [31, 33]. A formative study is also deemed necessary to gain an in-depth understanding of local dynamics in terms of social relations and stigma, and to design the practical implementation modalities (seed selection, type of compensation, place of interviews, etc.) A bootstrap approach has commonly been employed in RDS, to generate confidence intervals around estimates as these are more appropriate for the complex sampling underlying this method and avoid too narrow confidence intervals [32]. To take into account the fact that active ties are maintained not necessarily with other abortion seekers but sometimes with friends of abortion seekers, we developed during the preparatory phases for the study-and tested through modelling- a *multiplex RDS design*. This RDS innovates by occasionally involving the member of another population in the referral chains [41], i.e. by asking respondents to recruit another abortion seeker (as in the classic RDS) *or* a person who is close to one or more abortion seekers.^5^

Compared to the ATPR, the RDS has an evident advantage: a sample of abortion seekers where equilibrium has been reached is in principle quasi-representative. Therefore, the data obtained through RDS can be used to estimate the size of the transmission and barrier bias for the ATPR, and are probably more reliable than correcting factors obtained from self-report. The results obtained through ATPR-before and after correction—can also be compared to those obtained through RDS. The formative study (qualitative and quantitative) done in RDS could also usefully be applied to the ATPR. On the other hand, RDS could integrate features inspired by the ATPR, like targeting a large sample of abortion seekers, and using social referents to reach abortion seekers. But the RDS can only be applied in localized sites, while the ATPR can be used at all levels.

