### Data collection: respondent-driven sampling

#### Recruitment, inclusion criteria and interview setting

When the ATPR is done, a different team of fieldworkers will start the RDS. To begin the RDS sample in the HDSS area, following the tested procedures, we will purposively select a sample of 8 to 12 women who reside in the area and have had abortions in the last 3 years as seeds to recruit our target population; they will be selected to represent the demographic, economic, residential and occupational diversity of the sites (see section on ethics in the discussion for details on seed recruitment). After providing informed consent, each seed will be interviewed face-to-face and provided with 3 coupons to recruit their peers who should meet the same inclusion criteria (reside in the site and have had an abortion, or in a multiplex design, reside in the site, and be close to someone who has had an abortion; pilot results will determine in which circumstances to recruit a social referent). Three coupons are given based on previous studies to avoid recruitment chains dying off at the beginning due to attrition. Coupons will be coded with a unique ID number so that recruiters can be linked to their recruits. They will also contain a phone number to call with enquiries, activation and expiry date. The research assistant will be allowed to join the respondent at the place the latter finds convenient for the interview; the interviewer will make sure the proposed place meets all confidentiality and privacy criteria before starting.

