##### Questionnaire

The questionnaire administered to RDS participants will include:Sociodemographic characteristics and reproductive history of the respondent.Abortion history including number and timing of any induced abortions, how the abortion was induced (provider, setting, method), gestational age, post-abortion complications, treatment obtained, stigma (to be skipped for non-abortion seekers in multiplex RDS)Questions to estimate the biases of the ATPR: apply the ATPR modules to count close relations, characteristics of close relations, whether they had abortions, whether they told the respondents, how it was induced and any medical sequelae. For abortion seekers the module also contains the following questions: whether these close relations know about their abortions (whether respondents told them directly, respondents suspect they know even when not told).Stigma: three stigma scales will be used: community level, personal attitudes and internalized.

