### Plans for analyses

The analyses will focus on the two network methods applied to measure abortion safety (RDS and ATPR). The ATPR and RDS will provide data on what methods women use to have an abortion, where they have abortions and with what kind of provider, what side effects and post abortion care seeking behaviours they report.

The *RDS data* will be analyzed using the Respondent-Driven sampling analysis tool (RDSAT) or alternative tools in Stata or R, modified to take into account the multiplex structure if needed. For each site, we will examine recruitment patterns amongst respondents, and generate both crude point estimates for the sample recruited and population adjusted estimates of variables of interest including: women’s demographic characteristics, the proportion of women obtaining abortions from different types of providers, those experiencing complications, those seeking care etc. Additional analyses may include multivariable analyses examining the relationship between abortions with various degrees of safety or care seeking for complications and sociodemographic variables. We will also estimate the transmission rate using information on the number of respondents' close relations and the number who know about her induced abortions and its sequelae. We will measure the barrier bias by comparing the network sizes/structure of RDS respondents to that of all women in the ATPR survey.

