Using the *ATPR data* and for each site, we will describe women’s demographic characteristics and that of their network of close relations. We will check which network-generating question yields the less selected sample of friends, and whether one question yields a sample that contains more abortion seekers, at constant characteristics. We will correct for selection bias. We will estimate the proportion of close relations obtaining abortions with different methods, different types of providers, those experiencing complications, those seeking care etc. We will do the same for women' self-reported abortions. For the ATPR point estimates, uncertainty intervals will be generated using a bootstrap or a pooled sample approach to account for the non-independence of the sample of women reported on [17]. Using the estimated transmission and barriers rates through the RDS (and perhaps self-report) and the generalized NSUM model, we will correct the ATPR estimates of the abortion rate if pertinent. We will analyze the correcting factors by socioeconomic level and stigma, to further our capacity to generalize these correction factors. We will further validate the ATPR estimates by applying ATPR to indicators drawn from the reproductive history collected for close relations and respondents (contraception), and by comparing the ATPR estimates to those from national estimates.

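### The transmission rate used to correct the ATPR abortion rate comes from RDS recruits, who are selected on someone knowing of their abortion, so it is likely too high and the corrected rate too low

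*Protocol article*

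**What the plan says.** Under Plans for analyses the article states: "We will also estimate the transmission rate using information on the number of" each RDS respondent's close relations and on how many of them know of her abortions. The numerator comes from the RDS questionnaire, which asks abortion seekers "whether these close relations know about their abortions", whether told directly or suspected to know.

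The use follows in the same section: "Using the estimated transmission and barriers rates through the RDS (and perhaps self-report) and the generalized NSUM model, we will correct the ATPR estimates", with the proviso that this is done if pertinent. The Background section on respondent driven sampling gives the reason: "the data obtained through RDS can be used to estimate the size of the transmission and barrier bias for the ATPR". It adds that such factors are probably better than those from self-report, because a sample at equilibrium is in principle quasi-representative.

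On entry to the sample, each seed is "provided with 3 coupons to recruit their peers who should meet the same inclusion criteria". In the multiplex variant a referent close to an abortion seeker may also be recruited. Seeds are found through key informants, who are asked whether they can locate women who have had abortions (Recruiting participants). Recruits are screened for eligibility after referral.

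The article puts network reach at about seven or eight abortion seekers in ten (Respondent driven sampling; Limitations of the study). It does not carry that figure into the transmission rate, and it does not say how a recruiter on the respondent's list is to be counted.

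**The concern.** The transmission rate needed for ATPR is an average over all women who had an abortion, including those who told no one. The RDS sample is selected on a closely related quantity, namely that somebody knew or suspected. This acts in two ways:

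- **Coverage.** Women whose abortion is unknown to everyone contribute a rate of zero to the true average but hardly ever enter the sample. More open women are also easier to reach.
- **The recruiter on the list.** Where the recruiter is a close woman aged 15–49, she can appear on the recruit's list and is then a knower by virtue of having recruited her.

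Both push the measured rate up. The observed ATPR rate is in effect divided by it, so the correction is too small. The finding that ATPR suffers little transmission bias (item 2c under Methods), and correction factors meant to be generalized, would both look better than they should.

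**Working it through.** The article states no transmission rate or corrected rate, so there is no figure of its own to reproduce. What can be checked is direction and size under stated assumptions.

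**Inputs from the article:** two close relations per respondent, and planning rates of 22 (rural Burkina Faso) and 48 (Kenya) abortions per 1000 women, from the ATPR sampling section; network reach 0.7–0.8. **Assumed:** the true transmission rate t, the share r of recruits whose recruiter is on their list, and how disclosure varies between women.

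**Basic relation.** Corrected rate = observed rate ÷ transmission rate, so corrected ÷ true = t ÷ (RDS rate).

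**1. Recruiter on the list, independent disclosure.** With k listed relations, RDS rate = r × (1 + (k − 1)t)/k + (1 − r) × t.

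| k | t | r | RDS rate | Corrected ÷ true |
|---|---|---|---|---|
| 2 | 0.5 | 1 | 0.75 | 0.67 |
| 2 | 0.5 | 0.5 | 0.625 | 0.80 |
| 2 | 0.7 | 1 | 0.85 | 0.82 |
| 2 | 0.7 | 0.5 | 0.775 | 0.90 |
| 3 | 0.5 | 1 | 0.67 | 0.75 |
| 5 | 0.5 | 1 | 0.60 | 0.83 |
| any | any | 0 | t | 1.00 |

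In the first row, true rates of 22 and 48 per 1000 would be reported as 14.7 and 32.0.

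Weighting does not remove this. Suppose inclusion is proportional to the number of listed knowers and each woman is weighted by its inverse. The estimate is then t/(1 − (1 − t)^k); for k = 2 and t = 0.5 that is 0.5/0.75 = 0.67, because women with no knower remain absent.

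**2. Recruiter off the list.** With independent disclosure there is no bias. If openness varies between women and the chance of entry is proportional to it, RDS rate = E[t²]/E[t]. For a mean of 0.50 this gives 0.67, 0.60 and 0.55 under Beta(1,1), Beta(2,2) and Beta(5,5), so corrected ÷ true is 0.75, 0.83 and 0.92.

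**3. Coverage alone, extreme case.** If reach is s and transmission is zero outside it, RDS rate ÷ t = 1/s, which is 1.25 to 1.43 for s = 0.8 to 0.7. Corrected ÷ true equals s: 22 becomes 15.4–17.6 and 48 becomes 33.6–38.4 per 1000.

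**4. What removing the recruiter does.** Under independence it restores t exactly: (1 + (k − 1)t − 1)/(k − 1) = t. With Beta(2,2) openness and k = 2, the rate is 0.80 with the recruiter and still 0.60 without her, against a true 0.50. If instead every woman tells exactly one of two relations, the rate is 0.5 with the recruiter (correct) and 0/1 = 0 without her. Removal can therefore over- or under-correct.

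**The case against.** Several points count against a stronger version of this concern.

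- **A reader might infer that the rate is inflated by construction for every recruit.** The article does not support that. Coupons can be passed on suspicion, since eligibility is checked later. With inclusion proportional to the number of listed knowers K among k, the excess is Var(K)/(k × E[K]), which is zero if every woman tells exactly one of two relations. Selective telling is plausible, since the article describes disclosure only to people bound to secrecy.
- **The recruiter need not be on the list.** The article says information goes to close relations and also to people who can help, including other abortion seekers. It gives no share for the overlap.
- **A reader might infer circularity** from "When these assumptions are met, there is no transmission bias". But Table 1 frames the RDS condition as ties among abortion seekers and the ATPR condition as respondents knowing of their friends' abortions. Meeting the first does not set the share of listed relations who know.
- **Self-report is a possible second source.** Item 2c names it, though the analysis section says only perhaps. It is free of coupon selection, but women who self-report are also likely to be the more open ones, so it is not a clean standard either.
- **The main aim is safety.** A uniform transmission factor rescales the rate and cancels from the safety proportions. The rate correction is itself conditional.
- **Reach is disclosed as a limitation.** Unreached women are described as having direct access to care or using common-knowledge methods. That is not the same as having told no close friend.

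These limit the size and the certainty. They do not remove the selection: entry generally depends on someone knowing or suspecting, and nothing in the article allows for it. Equilibrium removes dependence on the seeds; it gives no chance of entry to women nobody knows about.

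**Conclusion.** Followed as written, the RDS transmission rate is likely biased upward and the corrected ATPR abortion rate downward, other biases being equal. The size cannot be determined from the documents. Under the independence model with two listed relations, the shortfall is 33% (true rate 0.5) or 18% (true rate 0.7) if recruiters are always listed, 20% or 10% if half are, and nil if none are. Variation in openness between women brings bias back even when the recruiter is off the list. The conclusion concerns the corrected abortion rate and the judgement on how much transmission bias ATPR carries. A reader might extend it to the ATPR safety proportions, but a uniform factor does not touch them.

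**What to change.** Before the RDS questionnaire is fixed, add one yes/no item per listed relation in the close-relations module: whether she is the person who gave the respondent the coupon. The existing link does not supply this. The article says "Coupons will be coded with a unique ID number so that recruiters can be linked to their recruits", but listed relations are recorded under nicknames or invented names, so the coupon number cannot show which of them is the recruiter.

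Then, in the analysis:

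- Report the transmission rate with and without the recruiter (in both numerator and denominator), using the RDS weights.
- Report beside these the rate from women who self-report an abortion in the random-sample survey. This needs the same knowledge question asked of them; the article names it only under the RDS questionnaire.
- Present the corrected ATPR abortion rate as a range across these. Add one sensitivity case that applies the article's own 70–80% reach with zero transmission outside it, labelled as an extreme assumption.
- State that the RDS rate with the recruiter counted is likely an over-estimate of transmission. Do not call the rate without her an upper or lower bound, since removal can err either way.

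The cost is one short item per relation, fewer relations per woman in one analysis (none for a woman whose only listed relation is her recruiter), and a wider reported range.

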Recruitment and questionnaire	Respondents in a random sample survey report anonymously on abortions occurring to close female relations 15–49, listed using a network generating question	Respondents in a random sample survey try to estimate the number of abortions which occurred in their entire network of acquaintances, whose size is estimated	A set of initial respondents (seeds) report on their own abortion and recruit other abortion seekers through their networks
Precision of data collected	Information on a set of finite close relations: information still relatively accurate	Not possible to ask for details on each abortion	Direct information from the abortion seekers: highest precision but still non-clinical knowledge
Assumptions	Respondent report accurately about abortions of friends (no social desirability bias) Respondents know about friends' abortions (no transmission bias) Abortion seekers have the same networks than general population (no barrier bias) Friends have the same networks than respondents (no selection bias) The network generating question may be biased towards friends with abortions	Respondent report accurately about abortions of entire network (no social desirability bias) Respondents know about abortions in entire network (no transmission bias) Abortion seekers have the same networks than general population (no barrier bias)	Abortion seekers self-disclose in an interview setting whose privacy is guaranteed by a network member (no social desirability bias) Abortion which constitute membership in the population must create connections amongst the members of the population, members must share active ties, and abortion is objectively verifiable (no transmission bias)
Correcting for biases	Transmission, barrier and selection biases have been corrected for in an ad hoc fashion so far. The social desirability bias cannot be corrected for	A model has been developed to correct for transmission and barrier biases; the social desirability bias cannot be corrected for but is acknowledged.*	If equilibrium is reached (if the characteristics of new recruits are independent of those of the abortion seeker who recruited initially), then assumptions are met and the sample is unbiased

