### The Anonymous Third-Party Reporting (ATPR) method (or confidantes' method)

ATPR was developed to collect quantitative data on induced abortion in restrictive contexts, by asking survey respondents to report anonymously on the recent abortions which occurred to a set of close female relations previously listed, including details on the abortion procedure and the complications experienced. The ATPR method is based on ethnographic work in Burkina Faso showing that information on abortions circulates in social networks in spite of this practice being strongly stigmatized, because women and couples cannot access abortion services otherwise [11]: information sharing is restricted to close relations and to people who can help in accessing abortion services, i.e. other abortion seekers or abortions providers. The ATPR defined close relations as people with whom respondents exchange private (i.e. secret, intimate) information; only female relations aged 15–49 (the demographic reproductive age group)—who can have abortions- are listed. Whilst the first tests of this method in Burkina Faso and Zambia and recent applications in PMA2020 surveys have yielded plausible results [12–14], four limitations have persisted. (i) First, different biases can affect ATPR results: *transmission bias -*respondents sometimes do not know about the abortions of their close relations-, *barrier bias* -abortion seekers' social networks may differ from that of average women- and *selection bias* -close female relations may have different networks than the general population-Up until now, these biases have been corrected for in an unsystematic way: different propositions coexist [14–19]. (ii) Second, it remains unclear in which contexts these biases are low and ATPR is applicable and in which contexts it is not the case [15, 16]. The existence of a transmission bias can be ascertained a priori, through a qualitative study documenting whether women with unintended pregnancies talk to close network members to locate underground abortion services [20]; but selection and barrier bias can be detected only when applying the method, suggesting the need for a quantitative pre-test. A fourth bias -*social desirability-* (not wanting to report on network member abortion or in the opposite overreporting such events) [15, 21] could also be probed in a pre-test. (iii) Third, the ATPR results ideally need to be validated, internally or externally. (iv) Fourth, the best standardized and unbiased network-generating question remains to be identified, as mentions of abortion in the presentation of the survey or in the network-generating question itself has been shown to inflate the estimates, and as a question focused on “secret sharing” may -perhaps- inflate the responses [18].^3^

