##### Pre-tests of the ATPR and RDS

In a location outside of the HDSS area (but similar in features), the questionnaire for the ATPR will be tested on 100 women aged 15–49. The questionnaire will include two successive network generator questions (the internationally validated “people you have discussed important matters with during the past year” as well as “up to three women you share secrets with”). The test of ATPR will advance knowledge on the network generating question best suited to investigate abortion and verify that the different biases (transmission, barrier, selection, social desirability) do not preclude the collection of data on abortion. The RDS pre-test will be conducted in a second location, also outside of the HDSS area, but also similar. The aim of the pre-test for the RDS is to fine-tune the RDS procedures (seeds, location for the interviews, etc.) and ascertain that abortion seekers in the study context accept to conduct interviews following peer-referral and to disclose their abortion in that context. Women recruited from 6 seeds following the RDS procedure (see more below) will be interviewed (up to a maximum of 30 individuals or 2 months of efforts). Among the six, three multiplex seed will be tested, in which respondents will be asked not only to recruit another abortion seeker but can also recruit somebody who knows an abortion seeker.

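### The transmission factor is measured on women the abortion seeker lists but corrects reports from women who list her; it is valid only under tie reciprocity, which is neither stated nor measured

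*Protocol article*

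**What the plan says.** **How transmission is measured.** In the RDS questionnaire (Questionnaire, under Data collection: respondent-driven sampling), participants "apply the ATPR modules to count close relations, characteristics of close relations, whether they had abortions", among other things. Abortion seekers are also asked "whether these close relations know about their abortions (whether respondents told them directly, respondents suspect they know even when not told". Plans for analyses then fixes the estimator: the team will "estimate the transmission rate using information on the number of respondents' close relations and the number who know about her induced abortions". Numerator and denominator are both counted over the seeker's own list.

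**How the factor is used.** Later in Plans for analyses, the transmission and barrier rates from the RDS, and perhaps from self-report, enter the generalized NSUM model to correct the ATPR abortion rate. The correction is conditional.

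**How ATPR reports arise.** In Table 1, survey respondents "report anonymously on abortions occurring to close female relations". The respondent makes the list, so a seeker's abortion reaches the data through women who list her.

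**What a close relation is.** The section on the ATPR method defines close relations as "people with whom respondents exchange private (i.e. secret, intimate) information". Two name generators are pre-tested (Pre-tests of the ATPR and RDS), and one of them is capped: "up to three women you share secrets with". Table 1 states the transmission assumption as "Respondents know about friends' abortions (no transmission bias") and adds accurate reporting, no barrier bias and no selection bias. Mutual listing is not among the assumptions.

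**The concern.** Let A be the abortion seeker and B the other woman. The ATPR needs the probability that B knows, given that B lists A. The plan measures the probability that B knows, given that A lists B. The two agree only under conditions that the article does not state.

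Disclosure is the seeker's decision. The article itself says that abortion information is confined to close relations and people who can help, and that seekers manage stigma by telling only those who will keep the secret. Women she names are therefore plausibly better informed than women who name her without being named back. Counting relations whom she only suspects of knowing could raise the measured factor further.

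Measuring transmission and barrier bias is aim 2c in Methods, and the analysis plan wants correction factors that can be generalized. An error of direction would therefore pass into later surveys. Taking the factor from self-report would not help if it is again built from the respondent's own list. RDS participants also say whether their relations had abortions and told them, but that covers only abortions already known to them, so it cannot show how often women who list a seeker remain unaware.

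**Working it through.** The article gives no transmission rate, reciprocity rate or correction factor, so there is no figure of its own to reproduce. The check is algebra on directed ties, with assumed inputs.

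**Notation**
- r: share of listed ties that are mutual.
- t_m: knowledge of the abortion on mutual ties.
- t_a: knowledge on ties that only the seeker lists.
- t_b: knowledge on ties that only the other woman lists.

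**Formulas** (seekers are listed as often as they list; barrier, selection and reporting errors are set aside)
- Planned factor: τ_out = r·t_m + (1−r)·t_a
- Needed factor: τ_in = r·t_m + (1−r)·t_b
- Uncorrected ATPR rate = true rate × τ_in
- Corrected rate as planned = true rate × τ_in/τ_out

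The ratio τ_in/τ_out equals 1 only if r = 1 or t_a = t_b.

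**Simple illustration.** Assume t_m = t_a = 0.8 and t_b = 0.4:
- r = 0.8: (0.64 + 0.08)/0.8 = 0.72/0.8 = 0.90, so 10% too low.
- r = 0.5: (0.40 + 0.20)/0.8 = 0.60/0.8 = 0.75, so 25% too low.
- r = 0.3: (0.24 + 0.28)/0.8 = 0.52/0.8 = 0.65, so 35% too low.

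**On the planning rates.** The sample-size section uses 22 per 1000 (rural Burkina Faso) and 48 per 1000 (Kenya). With t_m = t_a = τ_out = 0.75 (assumed):

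| r | t_b | τ_in | ratio | corrected, true 22 | corrected, true 48 |
|---|---|---|---|---|---|
| 1.0 | any | 0.75 | 1.00 | 22.0 | 48.0 |
| 0.8 | 0.40 | 0.68 | 0.91 | 19.95 | 43.5 |
| 0.6 | 0.40 | 0.61 | 0.81 | 17.9 | 39.0 |
| 0.4 | 0.20 | 0.42 | 0.56 | 12.3 | 26.9 |
| 0.6 | 0.75 | 0.75 | 1.00 | 22.0 | 48.0 |
| 0.6 | 0.90 | 0.81 | 1.08 | 23.8 | 51.8 |

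**Range.** For τ_out from 0.70 to 0.80, r from 0.4 to 0.8 and t_b from 0.2 to 0.6, the ratio runs from 0.55 to 0.97. With t_b = 0.9 it runs from 1.03 to 1.17. The choice of 0.70 to 0.80 borrows the article's order of magnitude of 7 or 8 in 10. There, that figure is a share of seekers for whom the RDS assumptions hold, not a rate per tie.

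**Simulation check** (directed network of 200,000 women):
- r = 0.6, t_m = t_a = 0.75, t_b = 0.4: true 22.0, corrected 17.8.
- r = 1: true 21.7, corrected 21.8.
- r = 0.6, t_m = 0.75, t_a = 0.6, t_b = 0.8: true 21.9, corrected 24.3, an over-correction.

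**Can ties be one-way?** The three-name cap limits how many women a respondent names, not how many name her. A woman named by five others can name at most three of them back, so at least two ties go unreturned even if all five exchange secrets with her.

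**The case against.** The strongest reply is that the tie is defined as two-way. Close relations exchange private information, and both generators use symmetric wording (sharing secrets, discussing matters with someone). On that view the two rates coincide. This stands as an implied assumption, but implied reciprocity is neither stated nor verified, and the cap can break it mechanically.

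The cap itself supports less than it may seem to. It belongs to one of the two generators, and planning assumes two close relations, so it need not bind for many women. Where it does bind, a confidante left out for lack of space may know just as often as one who was named, which pulls the two knowledge rates together.

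A reader might infer that the correction is bound to under-correct. The documents do not support that: they give no reciprocity or per-tie knowledge figure, and the working shows zero bias and over-correction under other inputs. The article also expects transmission bias among close relations to be low.

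The article is condensed. It announces five questionnaire sections and describes four, and the NSUM equations lie in a cited source. A reciprocity item could therefore exist unseen, and how the model treats tie direction cannot be judged here. But the estimator's numerator and denominator are stated, so the point does not rest on missing detail.

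The consequence is also limited. The correction concerns the abortion rate, is conditional, and leaves the RDS safety estimates untouched. Comparison with national estimates and the contraception check could reveal a discrepancy, but they would not isolate this cause.

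**Conclusion.** The point holds as an untested condition on a stated estimator. The planned factor describes ties listed by the seeker, and the rate it corrects rests on ties that list her. It is valid if ties are reciprocal or if knowledge is equal on both kinds of one-way tie.

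If neither holds, under-correction is the likelier direction because the seeker chooses whom to tell. It is not certain, and the barrier factor, also taken from listed networks, affects the net error. The 10% to 35% shortfalls illustrate assumed inputs and are not estimates for these sites. The matter should be settled before the instruments are final, because reciprocity that was never asked about cannot be recovered in analysis.

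**What to change.** 1. Add one yes/no item per listed relation, in both the ATPR and the RDS network modules, asking whether that woman also confides in the respondent. Place it after the name generators and the abortion questions so that it does not prime responses; the article itself notes that a secret-sharing focus may inflate them.
2. State reciprocity, or equal knowledge on both kinds of one-way tie, as an assumption of the correction.
3. Report the share of reciprocated ties by generator question, as part of choosing the best generator (aim 2b).
4. Show the corrected rate on all ties. Alongside it, give a sensitivity analysis restricted to perceived-mutual ties in both the factor and the rate, and a second over a range of r and t_b.

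**Cost.** Interviews become slightly longer, and the mutual-tie analysis has wider intervals because it uses fewer relations. The problem is only partly removed: one party reports the mutuality, and a capped list stays directional even among perceived-mutual ties. The mutual-tie result therefore belongs in a sensitivity analysis and should not replace the all-ties result.
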